### Intervention and control

The intervention is an individualised physical activity behaviour change programme. The intervention will be delivered by neurophysiotherapists with expertise in MS over a 12-month period. Because each programme is specifically created for each individual, components of the intervention may vary between participants. However, there are three consistent features: behaviour change strategies, recommendations for physical activity, and ongoing neurophysiotherapist support. After randomisation, participants in the intervention group will undergo a tailored intake by a neurophysiotherapist, which will serve as the foundation for the individualised approach. At the initial intake, neurophysiotherapists will evaluate the participants’ individual attributes and physical activity needs in addition to a general physiotherapy assessment (e.g., MS symptoms and functional levels) to create personalised programmes. This initial intake may occur over one to three sessions and in variable formats, depending on the participants’ needs. To promote consistency, neurophysiotherapists will be trained in the Behaviour Change Wheel [28], the BCTT [14], and the Social Cognitive Theory of Behaviour Change, including correlates and determinants of physical activity behaviour in MS [20]. All training of the neurophysiotherapists was done with a standardised programme and delivered by the same instructor.

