### Study outcomes

The primary outcome is the change in physical activity level, as measured by the change in the GLTEQ score from baseline to 12 months. The GLTEQ is a validated self-reported measure of physical activity with sensitivity to detect change in MS exercise interventions [23, 24]. The GLTEQ requests activity levels in the week prior (minimising recall bias), is easy to administer, demonstrates good test-retest reliability in ambulatory individuals with MS, and correlates with other more costly and/or less convenient measures of physical activity in MS, such as accelerometers [32]. The total GLTEQ score is calculated according to the number of self-reported strenuous, moderate- or mild-intensity physical activity in 15-minute time blocks over the week. A total leisure activity score is then computed, which includes a correction for the estimated metabolic demands associated with these intensity levels. The total GLTEQ score (range, 0–119) is recommended for use in physical activity research in MS [25], with higher scores indicating greater activity levels. A score > 23 is considered sufficiently active for substantial health benefits [23, 25].

Secondary outcomes include the change in patient-reported outcome measures assessing MS-specific symptoms, confidence and quality of life. The Multiple Sclerosis Impact Scale v2 [33] is a self-administered questionnaire evaluating patient-perceived physical and psychological impact of their MS. The Multiple Sclerosis Self-Efficacy Scale is an MS-specific, self-reported, self-efficacy measure with strong psychometric properties [34]. The 18-item version will be used whereby participants rate their level of confidence regarding components of disease management using a 10-point scale (very uncertain to very certain). Self-efficacy has been identified as one of the most consistent correlates of physical activity [35]. The Exercise Self-Efficacy Scale [36] is a validated and reliable measure for MS. It is a patient-reported ordinal six-item measure whereby items are rated on a scale of 0 (not at all confident) to 100 (highly confident) and averaged to obtain a total score. All study outcomes will be measured at baseline and at months 3, 6, 9 and 12 in both study groups (Fig. 1). To avoid anticipation of surveys potentially influencing responses, participants will only be informed that they will receive survey requests at random times over the study period.

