### Analyses

Baseline data collection will include both demographic and MS-related information (Table 1); the same information will be collected at the end of the 12-month study period for all participants. All analyses will follow the intention-to-treat principle. The primary outcome will be analysed with repeated measures analysis of variance (ANOVA) and mixed effects models to compare GLTEQ scores between the intervention and control groups at 12 months. A mixed effects model will incorporate missing data under the assumption of missing at random. Although the GLTEQ is an ordinal scale, we will treat it as continuous because this is common practice for this measure [37] and will allow comparisons with the existing literature. Further within-subject effect comparison at 12 months will be done using ANOVA. The group-by-time interaction will be explored using a mixed effects model after controlling for potential covariates. Similar analyses will occur for the secondary outcomes.

**Table 1 Tab1:** Baseline data collection variables

Variable	
Age (years)	
Sex	
Male	
Female	
Height	
Weight	
BMI	
Within normal limits	
Under normal limits	
Over normal limits	
Medical history	
Osteoarthritis	
Osteoporosis	
Coronary heart disease	
Stroke	
Diabetes	
Chronic respiratory disease	
Parkinson disease	
Cancer	
Other (list)	
Residence	
Urban	
Rural	
Type of MS	
Relapsing-remitting	
Secondary progressive	
Primary progressive	
Progressive relapsing	
Unknown	
Year of MS onset (e.g., first symptom)	
Year of MS diagnosis (by a neurologist)	
Most recent relapse (month/year)	
Walking aid or assistive device required?	
No	
Yes (if yes, list type)	
Employment	
Full-time (≥36 hours weekly)	
Part-time	
Casual	
Unemployed due to MS	
Retired	
Any falls in past 6 months?	
No	
Yes (frequency and severity)	
Disease-modifying therapy use	
Never	
Past (list)	
Current (list)	
Hospital Anxiety and Depression Scale (HADS) score	
Timed 25-ft walk (seconds)	
Nine-hole peg test (seconds)	
Symbol Digit Modality Test score	
Godin Leisure-Time Exercise Questionnaire score	
Multiple Sclerosis Impact Scale-29 v2 score	
Multiple Sclerosis Self-Efficacy Scale score	
Exercise Self-Efficacy Scale score	

*BMI* body mass index, *MS* multiple sclerosis

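### The only falls item the article describes, asked at baseline and month 12 with a 6-month look-back, does not cover the first 6 months of the intervention

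*Protocol article*

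**What the plan says.** Table 1 in the Analyses section, headed "Baseline data collection variables", includes the item "Any falls in past 6 months". A participant who answers yes is asked for frequency and severity. On timing, the text above the table says that "the same information will be collected at the end of the 12-month study period for all participants".

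The intervention lasts a year. Under Intervention and control: "The intervention will be delivered by neurophysiotherapists with expertise in MS over a 12-month period".

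The interim surveys are described for outcomes. Under Study outcomes: "All study outcomes will be measured at baseline and at months 3, 6, 9 and 12 in both study groups". Falls are not named there. The primary outcome is change in GLTEQ, and for the rest the article says: "Secondary outcomes include the change in patient-reported outcome measures assessing MS-specific symptoms, confidence and quality of life".

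The neurophysiotherapist encounter forms described under Intervention and control apply to the intervention arm only. Their named fields are how contact was made, what was delivered and how long it took.

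**The concern.** The look-back does not fit the interval between the two askings. A 6-month history is a sensible descriptor at baseline. Asked again 12 months later, it leaves a 6-month hole between the two windows, and the hole is the first half of the intervention. In that half, people enrolled because they were inactive, some of them walking with aids, start the programme and build up their activity.

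This is not a complaint about detail left out of a condensed article. The article prints the item, its look-back and its two time points, and together these do not span the study period.

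What is at stake is descriptive. Falls are a natural thing to report by arm in a trial that gets inactive people with MS moving. A summary built from this item would describe only the later half of the year. If starting activity led to falls, such a summary could show no difference between arms because the relevant months were never asked about.

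**Working it through.** **Coverage.** The plan states no figure to reproduce, so the check is one of intervals. An item asked at month t with look-back L covers months t - L to t.

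- Inputs: L = 6 (Table 1); t = 0 and t = 12 (Analyses); study period 0 to 12 (Intervention and control).
- Asked at month 0: covers -6 to 0.
- Asked at month 12: covers 6 to 12.
- On-study months covered: 6 of 12 (50%). Uncovered in both arms: 0 to 6.

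This takes assessments to fall at months 0 and 12 and the intervention to start at about baseline. A shift of a few weeks still leaves about half the period uncovered.

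**Alternatives, by the same rule.**

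| Asked at month | Look-back (months) | On-study months covered |
|---|---|---|
| 0, 12 (as stated) | 6 | 6 of 12 |
| 0, 6, 12 | 6 | 12 of 12 |
| 0, 12 | 12 at the final form | 12 of 12 |
| 0, 3, 6, 9, 12 | 3 | 12 of 12 |

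**Fallers missed.** The documents give no fall rate, so this part rests on assumptions. Let p be the proportion falling in any half-year, the same in both halves, and r the within-person correlation between halves. Those who fall only in months 0 to 6, and so appear as non-fallers at month 12, are p(1 - p)(1 - r) of participants. Those who fall at any time in the 12 months are p + p(1 - p)(1 - r).

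Completers per arm: 120 participants and 20% dropout are in the Analyses section; 1:1 allocation is assumed. 120 / 2 × 0.80 = 48.

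| p | r | Fall only in months 0-6 | Per arm (of 48) | Share of 12-month fallers missed |
|---|---|---|---|---|
| 0.30 | 0 | 0.30 × 0.70 = 0.21 | 10 | 0.21 / 0.51 = 41% |
| 0.50 | 0 | 0.50 × 0.50 = 0.25 | 12 | 0.25 / 0.75 = 33% |
| 0.30 | 0.5 | 0.21 × 0.5 = 0.105 | 5 | 0.105 / 0.405 = 26% |
| 0.50 | 0.5 | 0.25 × 0.5 = 0.125 | 6 | 0.125 / 0.625 = 20% |

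If falls cluster at start-up, the loss grows. For example, with 0.50 falling in months 0 to 6, 0.30 in months 6 to 12, and independence, 0.50 × 0.70 = 0.35 of participants are missed, or about 17 of 48.

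**The case against.** The strongest reply is that the item is only a descriptor. Table 1 is a list of baseline variables, falls are neither a primary nor a secondary outcome, and the Analyses section names no falls comparison. Asking for a 6-month history at both ends gives a like-for-like snapshot, and it becomes deficient only if someone reads it as a cumulative safety record. This stands in part: no stated analysis or conclusion depends on the item, which limits the weight of the point. It does not remove the mismatch, because the item is collected again at the end of the trial from everyone, and its obvious use there is to describe falls during the trial.

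A second reply is that Table 1 lists variables and is not the questionnaire, so the month-12 wording could differ. That is possible, but the text says the same information is collected, and the plain reading keeps the 6-month window.

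A third is that the size depends on an assumed fall rate and on independence between halves, whereas the same people tend to fall repeatedly. This stands, and is why the correlated case is shown. The coverage gap itself depends on neither assumption.

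A reader might go further and infer that no fall in the first 6 months is recorded anywhere. The documents do not support that. The schedule in Fig. 1 is not shown, the article condenses a fuller protocol, adverse-event collection is commonly left to that protocol, and the Monitoring section mentions monitoring of participants without detail.

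**Conclusion.** The point holds as a mismatch between look-back and interval. The one falls item described covers 6 of 12 on-study months and omits the start-up half in both arms. That rests only on the stated wording and timing. The count of missed fallers is illustrative: about 10 to 12 per arm at 30% to 50% per half-year with independence, about 5 to 6 at a correlation of 0.5, and more if falls concentrate early.

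The consequence is limited. The primary and secondary analyses are untouched, and falls in months 0 to 6 may be captured by a route the article does not describe. The intervention-arm encounter forms would not by themselves fill the gap, because controls have no equivalent.

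Three other inferences should be resisted:

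- The low-risk statement under Monitoring is an advance reason for having no monitoring committee. It is not a conclusion that the month-12 falls data are meant to support.
- The entry "Most recent relapse (month/year)" in Table 1 might look like a parallel fault. Asked at month 12, it still shows who had at least one on-study relapse. Only repeat counts are lost, and no relapse analysis is planned.
- Participants who leave before month 12 lack all month-12 data. That is ordinary attrition and not a defect of this item.

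**What to change.** Ask the existing falls item, unchanged, at the month-6 survey that both arms already receive. This gives 12 of 12 months of coverage for participants still answering, adds no recall burden beyond 6 months, and keeps the baseline and month-12 questions comparable. Report falls by randomised arm over the full 12 months.

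Timing allowed this when the article appeared. Enrolment began on 19 July 2019, so the earliest month-6 survey fell due about 19 January 2020, after publication on 2 December 2019. For anyone already past month 6, have the month-12 form also ask about falls since joining the study, and accept the longer recall.

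If the full protocol already records falls in months 0 to 6 in both arms, it is enough to say where.

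The cost is one or two added survey questions, a slightly longer questionnaire and a minor amendment.

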## Methods/design

### Study design and setting

The IPAC-MS (Individualized Physiotherapy and Activity Coaching for Multiple Sclerosis) study is a prospective, single-blind, parallel-group, randomised controlled trial conducted in the Canadian province of Saskatchewan. The study is designed as a superiority trial and is a collaborative effort of interdisciplinary researchers, clinicians, and patient and family advisors Additional file 1.

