### Randomisation and blinding

All consenting participants who have completed a baseline assessment will be stratified into one of three categories based on their baseline GLTEQ score (< 9, 9–17, ≥ 18). Participants from each of the three strata will be randomly assigned to either the intervention or control group by a centralised telephone request to a study coordinator not involved in data collection or analyses. Randomisation lists were computer-generated in blocks of 4 to help achieve balance in the groups. The randomisation list was created prior to participant recruitment by a research team member not involved in data collection or analyses. Given the nature of the intervention, only the outcome assessors involved in the data collection will be blinded to the study group.

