Using a conservative effect size of 0.3 for the primary outcome (change in GLTEQ), a power of 80%, and an alpha of 0.5, we estimate that 120 participants are needed for this study, allowing for 20% dropout. All statistical analyses will be conducted by the study biostatistician with use of SAS software (SAS Institute Inc., Cary, NC, USA), and all study data will be managed in REDCap (Vanderbilt, v6.7).

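### The sample size paragraph prints an alpha of 0.5, and reading it as 0.05 does not rescue it: if the effect of 0.3 is Cohen's d, 120 participants give about 31% power, not 80%

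*Protocol article*

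**What the plan says.** The protocol article gives its sample size in one sentence at the end of the Analyses section. It opens "Using a conservative effect size of 0.3 for the primary outcome (change in GLTEQ" and then sets out the remaining inputs and the result: "a power of 80%, and an alpha of 0.5, we estimate that 120 participants are needed for this study, allowing for 20% dropout".

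Related statements elsewhere in the article:
- Study design and setting: "The study is designed as a superiority trial".
- Under the outcomes heading, the endpoint is defined thus: "The primary outcome is the change in physical activity level, as measured by the change in the GLTEQ score from baseline to 12 months".
- Randomisation and blinding: two groups, three strata by baseline GLTEQ, and "Randomisation lists were computer-generated in blocks of 4 to help achieve balance in the groups".
- Analyses: the primary comparison is between groups at 12 months, by repeated measures ANOVA and mixed effects models.

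The article gives no other alpha. It does not state sidedness, an SD, the metric of the 0.3 or a within-subject correlation.

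**The concern.** A significance level of 0.5 is not credible for a superiority trial. A reader's first thought is that a zero was dropped and 0.05 was meant. If that were all, putting in 0.05 should bring back a figure near 120. Under the usual meaning of an effect size for a two-group difference in change, it does not: the requirement becomes several times larger.

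The stated power is at stake. Anyone who silently corrects the alpha will still believe that the trial had 80% power for an effect of 0.3. Under the d reading, a non-significant result would then be taken as fair evidence against an effect that the trial had less than one chance in three of detecting.

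**Working it through.** **Inputs.** From the sample size sentence: effect 0.3, power 80%, alpha 0.5 as printed, N = 120, dropout 20%. Assumed because not stated: 1:1 allocation (two groups, blocks of 4), a two-sided test, and 0.3 as Cohen's d on change in GLTEQ. The last assumption is relaxed in step 5.

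**Formulas.** Two-sample t-test with n per arm, df = 2n − 2 and noncentrality δ = d·√(n/2). Power = P(T > c) + P(T < −c), where T is noncentral t and c is the 1 − α/2 quantile of central t. Randomised N = 2n/(1 − 0.20).

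**1. The plan's figure with its printed inputs (d = 0.3, α = 0.5).**
- n = 47: power 0.798. n = 48: δ = 0.3·√24 = 1.470, c = 0.677, power 0.802.
- So 48 per arm, 96 evaluable, and 96/0.8 = **120**, which matches.
- The match depends on the exact calculation with both rejection tails. The wrong-direction tail contributes 0.016 of the 0.802. The usual normal approximation counts one tail and gives 52 per arm, and 104/0.8 = 130.

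**2. The same inputs at two-sided α = 0.05.**
- n = 175: power 0.799. n = 176: power 0.801.
- So 176 per arm, 352 evaluable, and 352/0.8 = **440** randomised.

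**3. Power of the planned trial at two-sided 0.05, d = 0.3.**

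| Analysed | n per arm | δ | c | Power |
|---|---|---|---|---|
| 96 (20% dropout) | 48 | 1.470 | 1.986 | 0.307 |
| 120 (no dropout) | 60 | 1.643 | 1.980 | 0.371 |

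**4. Effect detectable with 80% power at two-sided 0.05.** d = 0.578 with 48 per arm; d = 0.516 with 60 per arm.

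**5. The other reading: 0.3 is Cohen's f.** For two equal groups d = 2f = 0.6. At two-sided 0.05, n = 44 gives 0.795 and n = 45 gives 0.804. So 90 evaluable, and 90/0.8 = 112.5, or **113** randomised. With 48 per arm, power is **0.829**.

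**6. Other levels with d = 0.3 (exact t, N = 2n/0.8).** Two-sided 0.10 gives 348 and two-sided 0.20 gives 253. One-sided 0.05 gives 348, 0.10 gives 253 and 0.20 gives 160. None is near 120.

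**7. Baseline adjustment.** Its effect depends on the scale of the 0.3.
- On the SD of change, where the article places it, ANCOVA multiplies the variance by (1 + r)/2, with r the baseline to 12-month correlation. With 48 per arm at 0.05, power for 0.3 is 54% at r = 0, 39% at r = 0.5 and 35% at r = 0.7. No r between 0 and 1 reaches 80%.
- On the SD of the raw 12-month score, the factor is 1 − r², and 80% would need r of about 0.85.

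The article states neither a raw-score scale nor a correlation.

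**The case against.** The strongest reply is that 0.3 is Cohen's f. The planned analysis is an ANOVA, for which f is a common effect size, and the metric is not named. On that reading 113 are needed. Rounding up to 120 would be ordinary, and 120 is also the first multiple of 12 above 113 (three strata in blocks of 4). A rank-test allowance for an ordinal scale comes close too: 44.6 per arm divided by an efficiency of 0.955 is 46.7, so 47 per arm, and 94/0.8 = 117.5, or 118. Power at 96 evaluable would exceed 80% and the 0.5 would be a plain misprint. This stands as a possibility and is why the 31% must be conditional. It does not clear the sentence, because the alpha would still be wrong and the metric still unnamed.

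Three stronger readings are tempting, and the document does not support them.
- *That 120 was derived from 0.5.* Step 1 is consistent with this but does not prove it. The match needs one particular method, and an f-based calculation followed by rounding also ends at 120.
- *That the trial will accept a 50% false-positive rate.* The 0.5 appears only as a sample size input. The analysis paragraph sets no such decision rule.
- *That d = 0.6 could not be called conservative.* That depends on effect sizes in cited work which the article does not report, so it cannot be judged here.

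A further reply is that repeated measures or baseline adjustment supply the missing power. An undisclosed high correlation, with the effect on the raw-score scale, could do so. The article states no such assumption and attaches 0.3 to change.

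**Conclusion.** The concern holds in conditional form. The printed alpha is an error under any reading. Once it is replaced by two-sided 0.05, effect 0.3, power 80% and N = 120 are mutually inconsistent if 0.3 is Cohen's d: the requirement is 440 rather than 120, or equivalently the trial has about 31% power, with a detectable effect nearly twice the stated one (0.58/0.3 = 1.9). If 0.3 is Cohen's f, the sample is adequate and the fault reduces to a misprinted alpha and an unnamed metric. The document does not show which was meant.

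These figures rest on 1:1 allocation, a two-sided test, 20% loss and an unadjusted comparison of change at 12 months. This is not detail that could be left to an analysis plan, because the article states a value and that value is wrong.

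**What to change.** Correct the sample size sentence and leave enrolment as it is (the Trial status section already reports it complete at proof review):
- State the significance level as two-sided alpha = 0.05.
- Name the metric of the 0.3, and any within-subject correlation that was assumed.
- Restate the power or detectable effect for 96 evaluable, according to the metric:
  - If d: *120 randomised, 96 evaluable after 20% dropout, give 80% power for a standardised difference of 0.58; power for 0.3 is about 31%, unadjusted.*
  - If f: *effect size f = 0.3 (d = 0.6); 96 evaluable give about 83% power at two-sided 0.05.*
- Give no baseline-adjusted figure unless both its scale (SD of the raw 12-month score or SD of change) and the correlation are stated. The two scales give different answers.

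The cost is one reworded paragraph in the protocol, carried over to any other place where the sample size is justified. No extra participants are needed. The drawback is that, under the d reading, the published power or detectable effect becomes less favourable.

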### Monitoring

This study, including the participant consent form, has received ethical approval from the University of Saskatchewan Biomedical Research Ethics Board. Because this is a low-risk intervention, no data monitoring review committee is required. However, the University of Saskatchewan Biomedical Research Ethics Board has the authority to audit the study at any time to ensure compliance with approved protocols. Monthly research meetings involving the research team will be held to discuss day-to-day management and organisation of the study, including participant recruitment, delivery of the intervention, and participant monitoring. Finally, a trial steering committee comprised of the principal investigators, co-investigators, patient and family advisors, funders, and other stakeholders will meet quarterly over the course of the study period to monitor the overall study conduct and progress.

